### Setting

In total, 21 rehabilitation teams of 4 mental health institutions across The Netherlands were included. The size and compositions of the teams differed: the team sizes ranges from 4 to 28 team members, and the number of service users they help in their day-to-day needs ranges from 9 to 35. Most of the team members were psychiatric nurses with a degree at bachelor or below bachelor level. All teams provide long-term daily clinical care in an inpatient setting to adult people diagnosed with a severe mental illness according to DSM-IV or DSM-5 criteria, depending on the date of diagnosis. The majority of the service users receiving treatment were diagnosed with schizophrenia or related psychotic disorders; other diagnoses included severe depression, bipolar disorder, personality disorder, and autism. The teams were different from those that participated in the randomized controlled trial evaluating the effectiveness of Cognitive Adaptation Training [7] but were similar with regard to the provided treatment, support, and living conditions. The teams aim to provide a combination of treatments such as pharmacotherapy, psychological, psychosocial, and nonverbal therapies. Examples are psychoeducation, cognitive behavioral therapy, trauma therapy, creative therapy, and work projects such as landscaping, catering, woodworking, and production work.

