### Recruitment and Allocation

 Two mental health institutions included in this study indicated that they were interested in Cognitive Adaptation Training before the start of the study. The managers of the rehabilitation teams of these mental health institutions and 2 other institutions were approached by the research group and were provided with information about the study. If they indicated that they were interested, an appointment was made to provide more in-depth information about the intervention, the research and the required investment in terms of time and effort. All managers of the participating mental health institutions were asked to sign a research statement. In this statement, the departments declared that the researchers and departments had sufficient expertise and facilities to conduct the research, that these facilities were available to the researchers, and that they would inform all people who were required to contribute to the research. In addition, a liability statement was included. The service users received both written and oral information about the research by the team members. All participants were asked to provide written consent to participation and were informed that their participation was voluntary and that withdrawal of consent was possible at any time without consequences.

To avoid contamination between the 2 treatment conditions, cluster randomization was applied at the team level. Teams were clustered if their members were situated in the same building or if they indicated that they interact with each other on a day-to-day basis. When these criteria did not apply, single teams were entered as a cluster. The teams were randomly allocated to either the experimental condition (multiple tailored implementation strategies) or control condition (single implementation strategies) by an independent staff member who blindly drew a ticket from a box containing a ticket for either condition.

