### Sample Size

Sample size was estimated for both intervention effectiveness of Cognitive Adaptation Training (based upon the Life Skills Profile) as well as implementation effectiveness (based upon the outcome variable Reach). To ensure enough power for both purposes, we used the highest estimated sample size. For intervention effectiveness, with a mean difference of 6 points on the Life Skills Profile (considered clinically relevant according expert opinions) and a standard deviation of 10.5 (based on the effectiveness trial of Cognitive Adaptation Training in residential settings [7], 78 service users needed to be included to detect significant improvements on the Life Skills Profile with a power of .8 and a significance level of .05. Accounting for a conservative attrition rate of 20%, a minimum of 98 service-users needed to be included in the study. For implementation effectiveness, based upon previous implementation research in the Netherlands [16], the expected proportion of service users reached in the experimental condition was set at 30%, compared to 5% in the control condition. To be able to detect a difference between conditions in proportion of service users reached with Cognitive Adaptation Training (with α=.05 and a power of .8), both groups (control and experimental) required a caseload of at least 34 service users each.

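### Both sample sizes (78 for the Life Skills Profile, 34 per arm for Reach) ignore the randomisation of teams, so the stated power of .8 does not hold at those sizes unless within-team correlation is negligible

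*Protocol article*

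**What the plan says.** Under Recruitment and Allocation, the protocol article states that "cluster randomization was applied at the team level" to avoid contamination, and that teams were merged into one unit under set conditions: "Teams were clustered if their members were situated in the same building or if they indicated that they interact with each other on a day-to-day". Under Setting, "21 rehabilitation teams of 4 mental health institutions across The Netherlands were included", and "the number of service users they help in their day-to-day needs ranges from 9 to 35".

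Under Sample Size there are two calculations, both at power .8 and alpha .05, with sidedness not stated:

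- **LSP:** "with a mean difference of 6 points on the Life Skills Profile" and "a standard deviation of 10.5", from which "78 service users needed to be included to detect significant improvements on the Life Skills Profile with a power of .8". Attrition of 20% raises this to 98.
- **Reach:** 30% expected in the experimental arm against 5% in the control arm, from which "both groups (control and experimental) required a caseload of at least 34 service users each".

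The larger of the two results is then adopted. The section mentions no ICC, design effect, cluster size or number of clusters. The Statistical Analyses section plans a three-level model with team at the top level and one-tailed tests of the fixed effects.

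**The concern.** When teams are randomised, users of the same team carry partly overlapping information, and the effective sample is smaller than the head count. Reach is especially exposed. It is the share of a team's service users who receive the intervention, and it depends on what that team and its champions do. A negligible within-team correlation is therefore unlikely, and the relevant cluster size is the whole caseload.

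The article does more here than leave detail to a fuller document. It prints complete calculations with their inputs, and the printed results leave no room for a clustering allowance. At stake is the statement that these sizes give 80% power. Anyone who judges a null finding against that statement, or sizes a similar cluster trial from it, would rely on a property the design does not have at those numbers.

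**Working it through.** **Step 1. Reproduce the LSP figure.** Inputs from Sample Size: difference 6, SD 10.5, so d = 6/10.5 = 0.571; power .8; alpha .05. A two-sample t test on independent subjects needs:

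- one-tailed: 38.6, so 39 per arm and 78 in total, which matches exactly (power at 39 per arm 80.4%);
- two-sided: 49.05, so 50 per arm and 100 in total, which does not match.

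Attrition: 78/(1 − 0.20) = 97.5, so 98. Attrition is the only inflation applied.

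**Step 2. Place the Reach figure.** For 30% against 5%, independent users, per arm:

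- two-sided: 32.3 (33) with unpooled variance, 35.1 (36) with pooled variance;
- one-tailed, pooled: 27.5 (28);
- one-tailed Fisher test: power .815 at 34.

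The 34 is not pinned to one formula, but it sits among the independent-subject answers. Under independence, power at 34 per arm (pooled normal approximation) is 87% one-tailed and 79% two-sided.

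**Step 3. Apply the design effect.** DE = 1 + (m − 1) × ICC, where m is the number of users analysed per team. Power is evaluated at n/DE per arm, using the t test for LSP and the pooled normal approximation for Reach. All values are one-tailed, as in Statistical Analyses. The ICC values and m = 20 are assumptions; 20 lies inside the stated 9 to 35.

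Two worked cells:

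- LSP, 78 spread over 21 teams: m = 78/21 = 3.71. At ICC .10, DE = 1 + 2.71 × .10 = 1.27, so 39/1.27 = 30.7 effective per arm and power is about 72%.
- Reach, m = 20, ICC .05: DE = 1 + 19 × .05 = 1.95, so 34/1.95 = 17.4 effective per arm and power is 62%.

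| One-tailed power | ICC .01 | .05 | .10 | .20 |
|---|---|---|---|---|
| LSP, 78 completers over 21 teams (m = 3.7) | 79% | 76% | 72% | 64% |
| LSP, 78 completers, m = 20 | 74% | 55% | 42% | 29% |
| Reach, 34 per arm, m = 9 | 85% | 75% | 66% | 52% |
| Reach, 34 per arm, m = 20 | 81% | 62% | 48% | 33% |
| Reach, 49 per arm, m = 9 | 94% | 88% | 80% | 65% |
| Reach, 49 per arm, m = 20 | 92% | 77% | 61% | 43% |

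The 49 per arm rows follow from the rule of adopting the larger estimate: 98/2 = 49.

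**Step 4. Size needed on the same one-tailed basis, m = 20.** DE is 1.19/1.95/2.90/4.80 at ICC .01/.05/.10/.20.

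- Reach: 27.5 × DE gives about 33/54/80/132 per arm.
- LSP: 77.1 × DE (77.1 = 2 × 38.56) gives about 92/151/224/371 completers in total.

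**Step 5. The 21 teams with full caseloads.** The total is 21 × 9 = 189 to 21 × 35 = 735 users, assuming equal teams and equal arms. The smallest case, m = 9, gives 94.5 per arm.

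- ICC .10: 94.5/1.8 = 52.5 effective per arm; one-tailed power 97% for Reach and 90% for LSP.
- ICC .20: 94.5/2.6 = 36.3 effective per arm; 89% and 78%.

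At m = 35 and ICC .20, 367.5/7.8 = 47.1 effective per arm, giving 95% and 87%.

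**The case against.** Four points weigh on the other side.

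- **The plan does not rest on 34 per arm alone.** It adopts the larger estimate, 98, or about 49 per arm. This stands and softens the Reach figures, as the table shows, but at caseload 20 power still falls below 80% from ICC .05 upward.
- **Clustering is handled in the analysis.** The planned model has team as a level. This stands: the fault concerns the stated power. It is no ground for saying that the type I error or the estimates are invalid.
- **The ICC is unknown and could be small.** This stands in part. At ICC .01 one-tailed Reach still exceeds 80% at 34 per arm with caseload 20. LSP has no such slack: at 80.4% under independence, it falls to about 79% at ICC .01 even when spread thinly over all 21 teams.
- **The trial included far more than the minimum.** This also stands, and it limits the conclusion.

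A reader might infer that the trial as run is underpowered, or that one to four teams per arm were thought enough (34/35 = 0.97; 34/9 = 3.8). The documents support neither. Twenty-one teams were included, the adopted minimum was 98, and full caseloads would give good power at ICC .10. Nor can adequate power be taken as shown. The full-caseload figures ignore the small number of clusters, unequal and merged teams, and non-consent, all of which lower power, and the number of consenting users is not given.

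**Conclusion.** The point holds for the stated sample-size justification. Both calculations treat service users as independent although teams or merged teams were randomised. For LSP this is an exact reproduction; for Reach it is a strong inference from a near match. Power of .8 at 78 completers and at 34 per arm is therefore not a property of this cluster design unless the ICC is negligible.

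The shortfall depends on the assumed ICC and on how many users per team are analysed. It runs from about one percentage point (LSP spread over 21 teams, ICC .01) to about fifty (LSP at 20 users per team, ICC .20). The conclusion stops short of the power of the trial as run, which cannot be settled without the ICC, the number of randomised clusters and the number of users analysed.

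**What to change.** Rewrite the Sample Size paragraph so that it:

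1. states one sidedness for both calculations, consistent with the planned test;
2. applies DE = 1 + (m − 1) × ICC to LSP and to Reach, with the source of the assumed ICC and an allowance for unequal cluster size;
3. gives the number of randomised clusters per arm, counting merged teams as one;
4. reports the power of the 21 included teams over an ICC range such as .01 to .20, with the number of users expected to be analysed;
5. no longer presents 78, 98 and 34 per group as sizes that give 80% power.

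The cost is one paragraph and a short calculation. No extra participants are needed, and the planned multilevel analysis is unaffected. The downside is that the stated power becomes less favourable.

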### Statistical Analyses

To measure demographic and baseline differences between the 2 groups, chi-square tests will be performed for categorical variables, and 2-tailed independent sample *t* tests will be performed for continuous variables using SPSS software (version 24.0; IBM Corp). To assess the implementation effectiveness over time (outcome evaluation), mean differences in outcomes between the 2 arms on the dimensions of the RE-AIM framework were assessed using multilevel modelling [40]. A 3-level model will be built with team (level 3), subjects (level 2), and assessment (level 1) entered as levels. Significance of the fixed regression effects will be tested using the 1-tailed independent sample *t* test (=.05). The content of the focus group meetings and process evaluations will be transcribed verbatim and analyzed using a combined approach of inductive and deductive thematic analysis in ATLAS.ti (version 8.0; ATLAS.ti Scientific Software Development GmbH).

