**Manager**						
	Recovery-oriented care	ROPI^i^	X	—	—	X

^a^LSP: Life Skills Profile.

^b^NOSCA: Nurses’ Observation Scale of Cognitive Abilities.

^c^CAT Fidelity: Cognitive Adaptation Training Fidelity Scale.

^d^Assessed for the teams in the experimental condition only.

^e^TCI: Team Climate Inventory.

^f^OCM: Organizational Climate Measure.

^g^EPBAS: Evidence-Based Practice Attitude Scale.

^h^MIDI: Measurement Instrument for Determinants of Innovation.

^i^ROPI: Recovery Oriented Practices Index.

### Experimental Condition: Round 1

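### The outcome model stops at the team although teams in shared premises or daily contact were randomised together, and its coefficient test is misnamed, so p-values may be too small

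*Protocol article*

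**What the plan says.** Recruitment and Allocation opens with "To avoid contamination between the 2 treatment conditions, cluster randomization was applied at the team level". It then defines the cluster: "Teams were clustered if their members were situated in the same building or if they indicated that they interact with each other". The contact meant is daily contact. The remaining teams stood alone: "When these criteria did not apply, single teams were entered as a cluster". Allocation was by blind ticket draw. Setting gives 21 teams in 4 institutions, each caring for 9 to 35 service users. The article does not state how many clusters resulted or how many held more than one team.

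Statistical Analyses assigns the RE-AIM outcomes to multilevel modelling and fixes the levels: "A 3-level model will be built with team (level 3), subjects (level 2), and assessment (level 1) entered as levels". It then names the test: "Significance of the fixed regression effects will be tested using the 1-tailed independent sample". The test meant is a t test, at .05. Separately, it names chi-square and two-tailed independent-sample t tests for demographic and baseline differences.

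**The concern.** Two statements in the same article do not fit together. Grouping before allocation means that all teams in a cluster receive the same arm from one draw. They were grouped because they share premises or daily contact, so their outcomes may well be more alike than those of unrelated teams. A model whose top level is the team counts each of them as separate evidence about the arm effect. If grouped teams are positively correlated, the standard error is too small and a false positive is more likely than the stated .05.

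The name of the test is a second fault. An independent-sample t test compares two sets of independent observations. A fixed effect in a three-level model is tested by dividing the coefficient by its model-based standard error, with degrees of freedom suited to the number of higher-level units. There are at most 21 such units here, so the choice matters.

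The abstract lists all five RE-AIM dimensions as primary outcomes, so this model carries the trial's main inference.

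**Working it through.** **Randomised unit against model level**

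| Team's situation | Unit allocated | Top level in the model | Match? |
|---|---|---|---|
| Alone in its building, no daily contact with another team | Team | Team | Yes |
| Shares a building or daily contact with other teams | Group of teams | Team | No |

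**Inputs**

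- From the article: 21 teams; one-tailed .05; 9 to 35 users per team; a minimum of 98 service users for the Life Skills Profile.
- Assumed, because the article does not give them: the cluster layout; cluster variance c and team variance t as shares of total variance (each 0 to .05); users analysed per team m = 5 or 20. The value 5 is close to 98/21 = 4.7, and 20 lies within the caseload range.

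The article has no type I error calculation of its own to reproduce.

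**Closed-form approximation** (one time point, equal team sizes)

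- Variance of a team mean: v = c + t + (1 − c − t)/m
- Correlation of two team means in the same cluster: r = c/v
- With k_j teams in cluster j: DE = 1 + (Σk_j²/21 − 1) × r
- True one-sided error of a team-level test: P(Z > 1.645/√DE)

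Upper case: c = .05, t = 0, m = 20. Then v = .05 + .95/20 = .0975 and r = .05/.0975 = .513.

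| Layout of 21 teams | Σk²/21 | DE | 1.645/√DE | Error |
|---|---|---|---|---|
| 21 single teams | 1.000 | 1.000 | 1.645 | .050 |
| 17 clusters (4 pairs, 13 single) | 29/21 = 1.381 | 1.195 | 1.505 | .066 |
| 14 clusters (7 pairs, 7 single) | 35/21 = 1.667 | 1.342 | 1.420 | .078 |
| 11 clusters (10 pairs, 1 single) | 41/21 = 1.952 | 1.488 | 1.348 | .089 |
| 8 clusters (5 triples, 3 pairs) | 57/21 = 2.714 | 1.879 | 1.200 | .115 |

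Lower case: c = .02, t = .03, m = 5. Then v = .05 + .95/5 = .24 and r = .02/.24 = .083. With 11 clusters, DE = 1 + .952 × .083 = 1.079, 1.645/√1.079 = 1.583, and the error is .057.

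**Simulation under no effect** (6,000 runs per scenario, one time point, equal team sizes), one-sided error at nominal .05:

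| Clusters | Team as top level, c = .02 to .05 |
|---|---|
| 17 (4 pairs) | .052-.067 |
| 14 (7 pairs) | .054-.076 |
| 11 (10 pairs) | .053-.091 |
| 8 (mostly triples) | .061-.122 |

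With c = 0, or with 21 single-team clusters, the team-level test stays at about .05 (.046-.058). Analysis at the randomised cluster gives .044-.061 throughout, that is, about .05 within simulation error. The simulation and the closed form agree closely.

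**The case against.** The strongest reply is that the article says randomisation was at team level, that single teams formed their own clusters where the grouping criteria did not apply, and that the model does include a team level. For those teams the model matches the design. This stands, and it limits the point to grouped teams. It does not remove the point, because the sentences that follow define grouping before allocation.

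A reader might infer that the p-values are definitely too small. The documents do not support that. Inflation needs both multi-team clusters and positive correlation between the teams within them, and the article reports neither.

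A reader might also infer from the words about an independent-sample t test that outcomes will be compared between individuals with clustering ignored. A literal test of that kind would give an error of about .06 to .23 in the same simulations. But the article attaches the test to the fixed effects of a three-level model, so the likelier reading is a mislabelled coefficient t test that already accounts for team. Plain unclustered tests are clearly stated only for baseline differences, which enter no outcome p-value. The .06 to .23 range therefore does not measure what is planned.

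Finally, the effect depends on how many people are analysed per team. Fidelity and the determinants interview come from local champions, of whom two are recommended per team, so inflation there should be smaller than for an outcome with 20 users per team. The upper figures should not be applied to every RE-AIM outcome.

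**Conclusion.** The point holds in limited form. The stated model omits the randomised unit wherever teams were grouped, and the stated test is wrongly named for a multilevel coefficient. Both are visible in the article's own text and are not details deferred to an analysis plan.

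The consequence is conditional. With cluster variance at 2-5% of the total and 5 or 20 users per team, the one-sided error is about .05-.09 when clusters are single teams or pairs. It reaches about .12 only when most clusters are triples and all between-team variance lies at cluster level. It is .05 if all clusters are single teams or if grouped teams share no extra correlation. These figures rest on assumed layouts and variance components and on a simplified single-time-point simulation. The correction should be made, but nothing shows that the main results would be invalid without it.

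**What to change.** 1. Make the randomised cluster the top random level, with team nested within it, then subject and assessment; or analyse cluster-level summaries.
2. Replace the reference to an independent-sample t test with a t test of the arm coefficient whose degrees of freedom reflect the number of randomised clusters (Satterthwaite or Kenward-Roger).
3. Report the number of randomised clusters and how many contain more than one team. If every cluster proves to be a single team, the model already matches the design and only the name of the test needs correcting.

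The article describes data analysis as ongoing, and no new data are needed beyond the allocation record. The cost is a revised model statement and somewhat wider confidence intervals where teams were grouped.

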## Methods

### Study Design

This study is a 2-arm multicenter cluster randomized controlled trial comparing the implementation program, consisting of tailored multifaceted implementation strategies to a preset program with single implementation strategies, using mixed methods. The total study duration was 14 months. The first 2 months are used to train the participating teams in Cognitive Adaptation Training. The assessments are administered at baseline (2 months; T0), 5 months (T1), and 8 months (T2). Long-term effects were assessed by a follow-up assessment at 14 months (T3).

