### Outcomes and Measures

The outcome evaluation of the implementation program was based upon the RE-AIM framework [18]. This framework describes implementation success as a combination of reach, intervention effectiveness, adoption, implementation, and maintenance. In addition to the instruments that were selected based upon the RE-AIM framework, the questionnaires described in Assessment of Barriers and Facilitators and Process Evaluation sections were also used as outcome measures.

*Reach* was measured by the proportion of service users who received Cognitive Adaptation Training in each team and by comparing these numbers between the 2 treatment arms. To detect possible selection bias, the representativeness of service users who received Cognitive Adaptation Training in the intervention condition was determined by comparing their demographic variables to those of the service users in the entire study population.

*Intervention effectiveness* refers to the clinical improvement of the service users as a result of Cognitive Adaptation Training. The effectiveness of Cognitive Adaptation Training was determined by the improvements of the service users on daily functioning and cognitive functioning measured by 2 observational questionnaires: Life Skills Profile [34] and the Nurses’ Observation Scale of Cognitive [35]. The Life Skills Profile consists of 39 questions on a 4-point scale (total score range: 39-156) and measures various aspects related to daily life activities: self-care; nonturbulence; social contact; communication; and responsibility. Results on the Life Skills Profile from the previous research [7] evaluating the effectiveness of Cognitive Adaptation Training revealed a significant effect for people receiving Cognitive Adaptation Training in addition to treatment as usual compared to treatment as usual only. The Nurses’ Observation Scale of Cognitive Abilities [35] measures cognitive functioning and includes 39 items (total score range: 0-121) subdivided into 8 cognitive domains (subscales): attention, perception, memory, orientation, higher cognitive domains, thoughts, language, and praxis. The Nurses’ Observation Scale of Cognitive Abilities is scored on a 4-point scale. Both the Life Skills Profile and Nurses’ Observation Scale of Cognitive Abilities have good psychometric properties [36,37].

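### For LSP and NOSCA, measured only at T0 and T3, the 3-level model most naturally reads as a change-score test that ignores differences in change between teams; adjusting T3 for T0, with a random effect for the randomised cluster, is safer and more efficient

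*Protocol article*

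**What the plan says.** Under Statistical Analyses, "mean differences in outcomes between the 2 arms on the dimensions of the RE-AIM framework were assessed using multilevel modelling", and the sentence sets this within an assessment of effectiveness over time. The structure is given in one line: "A 3-level model will be built with team (level 3), subjects (level 2), and assessment (level 1) entered as levels". Fixed effects are to be "tested using the 1-tailed independent sample" t test at .05.

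Table 1 marks LSP and NOSCA at T0 and T3 and at no visit between. Under Outcomes and Measures, these two scales alone define intervention effectiveness, which is "determined by the improvements of the service users on daily functioning and cognitive functioning". The Abstract lists intervention effectiveness among the five primary outcomes. Under Recruitment and Allocation, "cluster randomization was applied at the team level", and teams that share a building or interact daily are grouped into one cluster.

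The article does not name the arm term (main effect or arm-by-time), a baseline covariate, or whether team has an intercept only or also a time slope. Its only stated use of baseline is a comparison of the arms.

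**The concern.** With assessment as level 1 and only two assessments, T0 must be one of the two outcome records; otherwise these scales have no level 1. Entering team as a level looks like protection for the cluster design. For a contrast in change it gives none if the team term is only an intercept, because a constant team effect subtracts out of T3 minus T0. What threatens the randomised contrast is that teams may change by different amounts over the 12 months between T0 and T3.

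The document makes such differences plausible. Teams range from 4 to 28 members and 9 to 35 users, both scales are observational ratings, and strategies in the experimental arm are tailored team by team. If the variation is left in the level-1 error, ordinary drift between teams can pass for a programme effect on a primary outcome.

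**Working it through.** **1. The plan's own figure.** Inputs from Sample Size: difference 6, SD 10.5, power .8, significance level .05. One-sided normal formula: 2 × (1.645 + 0.842)² / (6/10.5)² = 37.9, so 38 per arm. The exact t calculation gives 39 per arm (power 0.804), which is 78 in total. Then 78/0.8 = 97.5, so 98. Both figures reproduce, one-sided, with no allowance for teams. With 21 teams, 98/21 = 4.7, so about 5 users per team is the planned scale.

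**2. What cancels.** For user i in team j at time t, let Y = fixed part + u_j + s_ij + e_ijt. Then T3 minus T0 = time effect + δ × arm + (e_ij3 − e_ij0). Both u_j and s_ij have gone. With complete pairs, the arm-by-time test equals a pooled t test on individual change scores. If the team effect also has a part that differs between T0 and T3, all users of a team share that part of the change, but the model counts it as independent.

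**3. Size.** The article gives none of the following, so all are assumed: ICC ρ, correlation c of the team effect between T0 and T3, user T0-T3 correlation r, and m users per team.

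- ICC of change: ρ_D = ρ(1−c) / [ρ(1−c) + (1−ρ)(1−r)]
- Design effect: DE = 1 + (m−1)ρ_D
- One-tailed type I error ≈ 1 − Φ(1.645/√DE)

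For m = 5 and r = 0.5:

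| ρ | c | ρ_D | DE | Type I error |
|---|---|---|---|---|
| any | 1.0 | 0 | 1.00 | 5.0% |
| 0.02 | 0.8 | 0.008 | 1.03 | 5.3% |
| 0.05 | 0.8 | 0.021 | 1.08 | 5.7% |
| 0.05 | 0.5 | 0.050 | 1.20 | 6.7% |
| 0.10 | 0.5 | 0.100 | 1.40 | 8.2% |

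Simulation (4,000 trials per setting) over ρ 0.02 to 0.10 and c 0.5 to 0.8 gave 5.3% to 9.1%. A separate simulation with r = 0.6 reached 9.5% at ρ = 0.10, c = 0.5. At 15 users per team that same setting gave 14.8%. If every user in caseloads of 9 to 35 were rated (average 22, so 22 × 21 = 462 users), the range was 6.9% to 19.9%. With c = 1 the simulated rates were 4.5% and 5.1% at 5 and 15 per team.

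**4. Standard errors.** Take ρ = 0.10, c = 0.5, r = 0.6, SD 10.5 (variance 110.25), and 10 and 11 teams of 5 (50 and 55 users).

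- Level-1 variance: 110.25 × (0.9 × 0.4 + 0.1 × 0.5) = 45.2
- Model standard error: √[2 × 45.2 × (1/50 + 1/55)] = 1.86
- ρ_D = 0.05/0.41 = 0.122 and DE = 1.49, so the true value is 1.86 × √1.49 = 2.27

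Fitted REML models (100 in each of two settings) agree: mean model standard error 1.82 to 1.83, against an actual spread of 2.26 to 2.36. T3 adjusted for T0 with a team random intercept gave 1.97 to 2.03, against 1.93 to 2.10. A team-level version of the T0-adjusted test held two-sided type I error at 4.9% to 5.5%. Its power for 6 points at 5 per team was 82% to 93% (ρ 0.05 to 0.10, c 0.5 to 1.0, r = 0.6).

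**5. Efficiency.** In units of one-occasion variance between users within team, a change score has variance 2(1−r) and a T0-adjusted score 1−r². At r = 0.5 these are 1.0 and 0.75.

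**The case against.** The strongest answer is that the article does not state the model criticised here. Its sentence names grouping levels for all RE-AIM dimensions at once, and arm-by-time with a team-level time slope fits it and removes the problem. Random slopes and covariates are also details that a condensed article may leave to a fuller plan. This stands so far as it forbids calling the model a stated error. It does not remove the point. Levels entered without further terms are ordinarily random intercepts, and for two time points that form does not protect the randomised contrast.

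The inflation also rests on assumed variances, and the larger rates need far more users per team than the planned minimum implies. That stands too, which is why the figure at about 5 per team leads.

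A reader might infer something stronger: that the arm effect is a main effect averaged over T0 and T3, which would turn a 6-point effect into about 3. The wording on mean differences between arms permits this in isolation. But the same sentence speaks of effectiveness over time, the outcome is defined by improvements, and maintenance is defined by differences between time points. All of these point to arm-by-time, so the documents do not support the diluted reading.

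**Conclusion.** A likely weakness that should be corrected, held with medium confidence. If the model has intercepts only and an arm-by-time effect, the estimate is unbiased but the standard error is too small whenever teams change differently. At about 5 users per team this raises the one-tailed error from 5% to about 5% to 9%, under the assumed ICCs of 0.02 to 0.10 and team correlations of 0.5 to 0.8. The rate rises with the number rated per team, which the article does not report. Separately, and whether or not teams drift, the change-score form gives up precision that adjustment for T0 would recover. The documents do not support saying that the analysis must be wrong, because a team-level time slope is not ruled out.

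**What to change.** For LSP and NOSCA, state one of two equally valid analyses:

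- T3 score on arm and individual T0 score, with a random intercept for the randomised cluster. That is the single team, or the group of teams where teams were joined before allocation. Test the arm coefficient with small-sample degrees of freedom, as there are at most 21 randomised units.
- The repeated-measures model with a common T0 mean in both arms, the arm difference at T3 as the effect, and a cluster-by-time random effect, again with small-sample degrees of freedom.

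The cost is wording: T0 is already collected and the article reports that analysis is still under way. There are two downsides. Users without a T0 score need the constrained-baseline form or a simple baseline imputation. The interval may also be wider than the intercept-only model would give.
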